After considering the needs of both the patients and clinicians, we hypothesized that the implementation of the new SEP strategy would help improve diabetes control for T1DM patients. However, a well-designed RCT is needed to assess the effectiveness of the newly developed app compared to usual care. The present protocol is proposed to serve this purpose. The detailed hypotheses of the RCT are that T1DM patients using the app, as opposed to usual care, will have better diabetes control in terms of HbA1c level, time in range (TIR), quality of life, self-efficacy, and psychological conditions.

This paper presents the details of the design of and protocol for the first RCT assessing the effectiveness of a new SEP based on mobile technology that specifically targeted the T1DM population in China. This study is innovative in that it compares the effectiveness of smartphone apps between usual care and automated, individualized app education to explore whether individualized treatment, as advocated by the latest guidelines [14], will bring any additional benefit to T1DM patients. The ultimate goal is to provide an effective and convenient approach for T1DM control and reduce the related disease burden in China, where the T1DM control status is far from optimal. The protocol of the trial is reported by following the items recommended by the Standard Protocol Items: Recommendations for Interventional Trials (SPIRIT) 2013 statement [15]. The final results will be reported after the RCT in line with the Consolidated Standards of Reporting Trials (CONSORT) 2010 Statement for reporting parallel group randomized trials [16].

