**Secondary outcome**			
Time in range (TIR)	×	×	×
Fasting blood glucose (FBG)	×	×	×
Systolic blood pressure	×	×	×
Diastolic blood pressure	×	×	×
Total cholesterol	×	×	×
High-density lipoprotein (HDL) cholesterol	×	×	×
Low-density lipoprotein (LDL) cholesterol	×	×	×
Triglycerides	×	×	×
Body mass index (BMI)	×	×	×
Adult diabetes quality of life (A-DQOL)	×	×	×
The type 1 diabetes self-management questionnaire	×	×	×
Summary of Diabetes Self-Care Activities Assessment (SDSCA)	×	×	×
Diabetes Empowerment Scale-Short Form (DES-SF)	×	×	×
Beck’s Depression Inventory (BDI)	×	×	×
State-Trait Anxiety Inventory (STAI)	×	×	×
Patients satisfaction	×	×	×
Adverse events^a^	×	×	×

^a^Adverse events will be collected every 4 weeks during the intervention period through a telephone interview

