#### Data analysis

The primary data analysis will be conducted by using data collected at week 24 under the intention-to-treat principle by including all the randomized patients in the data analysis. Missing data will be filled in with a multiple imputation method under the “missing at random” assumption [35]. Any substantial difference in baseline characteristics will be adjusted with mixed-model regression analysis. Between-group differences will be assessed for the smartphone app group versus the routine care group. Relative risk reductions with 95% CIs will be calculated for dichotomous outcomes. The mean difference with standard deviation (SD) will be used to measure the treatment effect for continuous outcomes.

Secondary data analysis will use data collected at week 12 and week 24. All analyses will follow the same template as the primary data analysis by using a mixed model to adjust for imbalanced baseline characteristics. Linear regression will be used for continuous outcomes, and logistic regression will be used for binary outcomes. Model assumptions will be checked by regression diagnostics for all regression models. Predefined moderators including psychological and psychosocial mediators (e.g., depression, anxiety, self-efficacy) will be examined for treatment interactions. The Bonferroni method will be adopted to adjust the significance level under the circumstance of multiple testing. Furthermore, longitudinal analysis in which data collected at baseline, week 12, and week 24 will be jointly analyzed with appropriate mixed models. The time point will be included as a categorical fixed factor with the first-order autocorrelation of the errors and random intercepts. Monthly data collected on HbA1c during the intervention period will be analyzed with similar mixed models.

A sensitivity analysis will be conducted by using per-protocol data and excluding those patients who drop out of the RCT. The results from the sensitivity analysis might provide some pragmatic evidence from the real world regarding the effectiveness of the smartphone app for controlling T1DM. All statistical tests will be two-sided, with *p* < 0.05 considered to indicate statistical significance.

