## Discussion

A robust and well-designed RCT will be conducted to determine the effect of an automated, structured education intervention based on an app and artificial intelligence; it has been developed in an evidence-based and culturally tailored manner for the Chinese population for the management of T1DM. The detailed research plan of the RCT is presented in this protocol.

Although evidence had established the effect of smartphone apps in diabetes care, the majority of apps had been developed for T2DM patients and targeted at populations outside of China [10, 11]. According to an updated systematic review [11], only seven trials provided evidence on the effect of smartphone apps among T1DM patients. Pooled results (pooled MD in HbA1c − 0.49%, 95% CI − 0.94 to − 0.04%, *I*^2^ = 83.29%) showed a promising benefit for using smartphone apps to manage T1DM. However, the results from the individual trials were substantially inconsistent (MD of HbA1c varied from − 1.17% [36] to 0.41% [37]), which explained the high level of heterogeneity (*I*^2^ = 83.29%) in the meta-analysis. Furthermore, the results also indicated that the effect of smartphone apps in type 1 diabetes care was still controversial and had a low quality of the evidence [11].

Hence, whether smartphone apps will provide benefits to T1DM patients has not yet been conclusively determined. Very limited effective apps are available for T1DM patients from China. We developed a smartphone app by specifically considering the cultural background and lifestyle of the Chinese population to assist self-management and meet the need for lifelong diabetes care in T1DM patients. In this study, we seek to determine the effectiveness of the newly developed app in type 1 diabetes care compared to routine care.

Moreover, we also plan to explore whether tailoring health education materials by considering the specific knowledge gaps of each individual patient will provide some extra benefits in reducing HbA1c and improving other psychological and psychosocial outcomes. This will facilitate the development of future smartphone apps. As advocated by the latest guidelines, strategies for diabetes management should promote individualized targets and treatments [14]. By including multiple secondary outcomes, this RCT has the chance to explore the potential mechanisms of smartphone apps in improving diabetes care. This will contribute to appropriate outcome selections for future RCTs in diabetes care.

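### Depression, anxiety and self-efficacy are called both moderators and mediators with no baseline restriction, and a completer analysis that cannot test missing at random is described as real-world evidence

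*Protocol article*

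**What the plan says.** All the analysis statements are in the Data analysis section of the protocol article.

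- **Primary analysis.** Week-24 data, intention to treat, all randomised patients, with multiple imputation under missing at random.
- **Interactions.** In the paragraph on secondary analysis: "Predefined moderators including psychological and psychosocial mediators (e.g., depression, anxiety, self-efficacy) will be examined for treatment interactions". That paragraph opens by saying that secondary analysis uses week-12 and week-24 data. It does not say which time point supplies the moderator.
- **Sensitivity analysis.** "A sensitivity analysis will be conducted by using per-protocol data and excluding those patients who drop out of the RCT". Its results, the article adds, "might provide some pragmatic evidence from the real world regarding the effectiveness of the smartphone app for controlling T1DM". No other sensitivity analysis is stated.

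Elsewhere, the Background hypothesises that app users will have "better diabetes control in terms of HbA1c level, time in range (TIR), quality of life, self-efficacy, and psychological conditions". Table 1 lists the depression, anxiety and self-efficacy scales as secondary outcomes at baseline, week 12 and week 24. The Discussion says that "this RCT has the chance to explore the potential mechanisms of smartphone apps in improving diabetes care".

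**The concern.** A moderator has to be unaffected by treatment, which in practice means measured before randomisation. A mediator is by definition changed by treatment. The plan gives both names to the same variables and sends them to an interaction test. That test addresses effect modification, not mediation. If follow-up scores are used, the model conditions on something the app is expected to move, and its treatment coefficient no longer estimates the app's total effect.

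The sensitivity analysis raises two separate problems. First, a set without drop-outs describes patients who stayed, and it loses the protection of randomisation. Calling it pragmatic real-world evidence invites readers to prefer the more selective estimate. Second, a sensitivity analysis beside a missing-at-random imputation should ask what happens if that assumption fails. Excluding the patients with missing data does not ask that.

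**Working it through.** **Design figures (Sample size estimation).** Effect 0.6, 110 evaluable patients, 20% drop-out. 110 / (1 - 0.20) = 137.5, rounded up to 138, or 69 per arm. The stated total reproduces. No SD is given. At 55 per arm, two-sided 5% and 80% power, the implied SD is 0.6 × √(55/2) / (1.96 + 0.84) ≈ 1.12. It is used below only as an assumption.

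**1. Which score enters the interaction?** Suppose the app shifts a score by *s*, and the within-arm slope of week-24 HbA1c on that score is *b*, equal in both arms (no true interaction). Then

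treatment coefficient = total effect - *s* × *b*.

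For a baseline score *s* = 0, so the coefficient stays at the total effect. For follow-up scores, with all parameters assumed:

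- *Scenario A.* The score shares an unmeasured cause with HbA1c but does not act on it; SD 1.12, *s* = 0.5. Within-arm covariance is 1.12 × (0.2 × 0.6 - 0.4 × 0.5) = -0.0896 and variance is 0.36 + 0.25 + 0.36 = 0.97, so *b* = -0.092. Coefficient: -0.60 - 0.5 × (-0.092) = **-0.55**.
- *Scenario B.* The score carries part of the effect (direct -0.40, through the score 0.5 × -0.4 = -0.20, total -0.60) and shares an unmeasured cause. With a score residual SD of 0.8, the within-arm variance is 0.36 + 0.64 = 1, so *b* = -0.4 - 0.5 × 0.6 = -0.70. Coefficient: -0.60 - 0.5 × (-0.70) = **-0.25**, which matches neither the total nor the direct effect. With residual SD 1.0 it is -0.29.

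Simulation agreed. With a baseline score the coefficient was -0.60 and the interaction test rejected in 5.1% to 5.3% of trials. With a follow-up score the coefficients were as above. The interaction test was not inflated: 4.2% in scenario A and 4.9% in scenario B, where the mean interaction coefficient was 0.00.

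**2. Can the completer analysis test missing at random?** Assume that 20% of each arm drop out without a week-24 HbA1c, that app patients who stay gain 0.6, that app drop-outs gain nothing, and that drop-out is otherwise unrelated to outcome. Imputation uses arm and baseline.

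| Analysis | Arithmetic | Difference |
|---|---|---|
| Full data, all randomised | 0.8 × (-0.6) + 0.2 × 0 | -0.48 |
| Planned imputation under missing at random | 0.8 × (-0.6) + 0.2 × (-0.6) | -0.60 |
| Completers only | -0.6 | -0.60 |

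A simulation with SD 1.12 and baseline correlation 0.5 gave -0.49, -0.61 and -0.61. The agreement of the last two is structural: when only the outcome is missing, imputing from arm and baseline carries the completers' relation over to the drop-outs. An imputation model that also uses week-12 HbA1c could recover part of the gap where that value was observed and already showed the lost benefit.

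A delta-adjusted imputation does expose the assumption. Adding δ to the imputed app-arm values gives -0.60 + 0.20 δ: -0.54 at δ = 0.3 and -0.48 at δ = 0.6. The last equals what control-based imputation gives here.

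**3. Is the completer estimate biased in itself?** Only under some conditions (SD 1.12, true effect -0.60). With drop-out unrelated to outcome, or 20% in each arm and equally related to it, the estimate stays at -0.60. With 10% drop-out in control and 30% in the app arm, and patients with worse HbA1c more likely to leave (correlation 0.3 to 0.5), it becomes -0.70 to -0.77.

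**The case against.** The strongest reply on the moderators is that the article never says follow-up scores will be used. The word predefined fits baseline scores, these are collected, and an interaction with a baseline score is valid. That stands: the defect is contradictory wording with the time point left open, not a demonstrated bias. A reader might infer that subgroup claims from this analysis would be artefacts. Neither the documents nor the simulations support that, since the interaction test kept its level even with follow-up scores. What moves is the treatment coefficient in that secondary model.

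On the sensitivity analysis, it is fair to say that the per-protocol set is secondary to an intention-to-treat analysis, that the real-world sentence is hedged, and that imputation detail belongs in an analysis plan not shown here. The first two points limit the seriousness, but the hedge does not correct the direction of the claim. On the third, the absence of a delta-adjusted analysis from an article would be no finding by itself. The point here is that the article does name a sensitivity analysis, and the one named cannot probe the assumption it sits beside.

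A reader might also infer from 0.60 / 0.48 = 1.25 that completers would show an effect 25% larger than the planned intention-to-treat analysis. That does not follow. The 20% is a withdrawal rate, drop-outs' week-24 values would be imputed under missing at random, and both planned analyses would then show about -0.60. The -0.48 needs the drop-outs' outcomes to be observed.

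**Conclusion.** The point holds in three parts.

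1. The moderator sentence contradicts itself and should be tied to baseline. If follow-up scores were used, the treatment coefficient could be distorted (-0.55 or -0.25 for a total of -0.60 in two assumed scenarios), and mediation would still be untested.
2. The real-world description is reversed: the intention-to-treat analysis is the pragmatic one. This needs no assumption.
3. The completer analysis cannot test missing at random. In the illustration it repeats the imputed result of about -0.60 when the full-data effect is about -0.48. This rests on 20% drop-out, an effect of 0.6 in those who stay, none in app-arm drop-outs, and imputation from arm and baseline.

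It would go too far to say that both analyses give biased effects. The first is valid with baseline scores, and the second is biased only when drop-out differs between arms and relates to outcome. That is plausible where patients know their arm, but it is not certain. The primary estimate is not shown to be wrong; what is weak is the check meant to support it.

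**What to change.** - Replace the moderator sentence with: treatment interactions are tested only with baseline depression, anxiety and self-efficacy scores. Any mediation analysis is separate and exploratory, for example week-12 mediator and week-24 HbA1c, adjusted for baseline.
- Relabel the per-protocol analysis as supplementary and delete the sentence that calls it real-world evidence.
- Make the sensitivity analysis of the primary outcome a multiple imputation that departs from missing at random: either shift imputed app-arm week-24 HbA1c in steps until the conclusion changes, or impute app-arm drop-outs from the control arm.

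The baseline scores are already in Table 1, so no new data are needed. The cost is a few sentences, a few lines of imputation code and one more analysis to report.

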#### Secondary outcomes

Due to the complex nature of T1DM, it is important to include a wide spectrum of outcomes to measure the treatment effect. Therefore, physiological parameters, psychosocial outcomes, and psychological outcomes are included in the secondary outcomes.

Time in range (TIR) of 70–180 mg/dL (3.9–10 mmol/L) will be used as a secondary outcome to overcome the inability of HbA1c to provide information on patients’ hypoglycemia, glycemic variability, or daily patterns of glycemia [23]. TIR is a newly recognized indicator of glycemic management by both clinicians [23] and patients [24]. TIR data will be collected using a continuous glucose monitoring system (iPro2, Medtronic). Data on other physiological parameters including fasting blood glucose (FBG), levels of cholesterol and triglycerides, blood pressure, and body mass index (BMI) will be also collected as the secondary outcome (Table 1).

The valid and reliable diabetes quality of life (DQOL) scale [25] is a widely used 46-item tool for assessing the quality of life related to diabetes in terms of three aspects: diabetes satisfaction (15 items), impact (20 items), and worry (11 items). Each item is answered on a 5-point Likert scale, with a score of 1 representing “always affected,” “always worried,” or “never satisfied” and a score of 5 indicating “no impact,” “no worries,” or “always satisfied”. A higher total score reflects a better quality of life. A Chinese version of the DQOL scale has been translated [26] and validated [27] in the diabetic population from mainland China and will be adopted in this trial.

Diabetes self-care behaviors will be assessed with the Summary of Diabetes Self-Care Activities (SDSCA) measure, which contains six behavior-related scales: general diet, specific diet, glucose monitoring, physical activity, foot care, and smoking. Absolute weekly frequency or consistency of diabetes self-care activities are scored with a scale ranging from 0 to 7, with higher scores reflecting better performance in self-care behaviors. The internal consistency reliability and construct validity of the SDSCA was supported by its psychometric test based on an adult diabetes population [28]. A validated Chinese version of the SDSCA is available for this trial [29].

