Patients’ diabetes-related psychosocial self-efficacy will be evaluated with the Diabetes Empowerment Scale-Short Form (DES-SF), which is a short form of the Diabetes Empowerment Scale developed based on the American population with type 1 or type 2 diabetes [30, 31]. A revised Chinese version is available for the mainland China population [32]. The Chinese version of the DES-SF includes 8 domains with 1 item for each, covering the need for change, making a plan, overcoming barriers, seeking support, maintaining optimism, supporting oneself, diabetes-related pressure relief, and making the appropriate choice according to individual conditions for self-diabetes care. Each item is answered on a 5-point Likert scale, with 1 indicating strongly disagree and 5 indicating strongly agree. The total score ranges from 8 to 40, with a higher total score reflecting better psychosocial self-efficacy.

Patient psychological status, including depression and anxiety, will be assessed with the Beck’s Depression Inventory (BDI) and the State-Trait Anxiety Inventory (STAI) respectively. The Chinese version of the BDI consists of 21 self-rated items [33]. Each item will be scored from 0 to 3, with a total score ranging from 0 to 63, and a higher score indicates more serious depression. The Chinese version of the STAI consists of two subscales to measure both state and trait anxiety states [34]. Each of the two anxiety states will be measured with a 20-item subscale, and each item will be scored from 1 to 4. The total score for both state and trait anxiety ranged from 20 to 80, with higher scores indicating more serious anxiety. Data on patients’ satisfaction will also be collected through verbal rating grading, which involves ordering a four series of adjectives from lightest to strongest satisfaction.

Patients’ engagement with the app will be measured in terms of communications with the clinician and the utilization of the smartphone app. Specifically, the number of messages with education materials sent to the patients, the number of and delay of in message responses, the number of video calls/phone calls with patients, the number of logs entered entries by patients, and the time spent in the diabetes SEP diabetes education module will be collected.

Safety-related outcomes, including hypoglycemic events, hospitalization, and emergency room visits, will be collected at each follow-up time point.

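### Single-step Bonferroni is valid for the multiple tests, but Holm's step-down version keeps the same 5% bound and never rejects fewer hypotheses; the gain for this trial is probably small

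*Protocol article*

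**What the plan says.** The second paragraph of the Data analysis section names the method: "The Bonferroni method will be adopted to adjust the significance level under the circumstance of multiple testing". It does not say which tests form the family, how many there are, or what the adjusted level is.

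The text around it allows several readings of the family:

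- The paragraph opens with "Secondary data analysis will use data collected at week 12 and week 24", so two time points are in play.
- The sentence just before the Bonferroni one reads "Predefined moderators including psychological and psychosocial mediators (e.g., depression, anxiety, self-efficacy) will be examined for treatment interactions", so interaction tests may be covered too.
- Table 1 lists 17 secondary rows, the last of which is adverse events. Without that row there are 16.
- Some rows hold more than one scale. For the self-care measure the article says "which contains six behavior-related scales: general diet, specific diet, glucose monitoring, physical activity, foot care, and smoking", and for anxiety "The Chinese version of the STAI consists of two subscales to measure both state and trait anxiety states".

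The section closes with a general rule: "All statistical tests will be two-sided, with *p* < 0.05 considered to indicate statistical significance". How that rule sits beside the Bonferroni sentence is a separate question and is not argued here.

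The reason given for measuring so many outcomes is that "it is important to include a wide spectrum of outcomes to measure the treatment effect". The Background hypothesises benefit on HbA1c, time in range, quality of life, self-efficacy and psychological conditions.

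**The concern.** Single-step Bonferroni compares every p-value with the same threshold, 0.05/m, even after other hypotheses in the family have been rejected. Once some are rejected, that threshold is stricter than control of the familywise error requires. Holm's procedure relaxes it step by step and needs no extra assumption.

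The issue arises here because the plan measures many outcomes and expects several to improve together, which is the setting in which a step-down procedure can help. What is at stake is some power for the secondary outcomes. Type I error control is not at stake: Bonferroni already provides it.

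**Working it through.** **The plan's own figure.** The Sample size estimation section inflates 110 patients for 20% drop-out: 110/(1 − 0.20) = 137.5, rounded up to 138. This reproduces. The article states no standard deviation. The one implied by 55 per arm, a difference of 0.6%, two-sided 5% and 80% power is

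SD = 0.6 × √(55/2) / (1.960 + 0.842) = 1.12%,

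so the implied standardised effect is about 0.6/1.12 ≈ 0.535. Applying this to the secondary outcomes is an assumption.

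**Why Holm never rejects less.** Order the p-values and compare the i-th smallest with 0.05/(m − i + 1), stopping at the first failure. Every such threshold is at least 0.05/m, so any p-value at or below 0.05/m passes under Holm as well.

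**Why the 5% bound holds.** Suppose m₀ hypotheses are truly null. The first true null that Holm rejects must be rejected no later than step m − m₀ + 1, where the threshold is at most 0.05/m₀. The chance that any true null has a p-value that small is at most m₀ × 0.05/m₀ = 0.05, whatever the dependence. Neither argument depends on m.

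**Thresholds for m = 16.** Bonferroni: 0.05/16 = 0.003125 for every test. Holm: 0.003125, 0.00333, 0.00357, … 0.025, 0.05.

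**Other readings of the family.** m = 17 gives 0.00294, m = 32 (16 outcomes at two times) gives 0.00156, and m = 34 gives 0.00147. Counting subscales or interaction tests would lower the level further.

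**Direct check of Bonferroni power.** The expected test statistic is 0.535 × √(55/2) = 2.806.

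- m = 16: Φ(2.806 − 2.955) = 44.1%.
- m = 32: Φ(2.806 − 3.163) = 36.0%.

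**Simulation.** Normal test statistics, pairwise correlation 0.3, equal effects of 0.535, 55 per arm:

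| Tests | True effects | Bonferroni power | Holm power | Extra true effects found per trial |
|---|---|---|---|---|
| 16 | 5 | 44.1% | 45.6% | 5 × 0.015 ≈ 0.08 |
| 16 | 8 | 44.0% | 47.1% | 8 × 0.031 ≈ 0.25 |
| 16 | 12 | 44.1% | 49.8% | 12 × 0.057 ≈ 0.68 |
| 16 | 16 | 44.0% | 54.5% | 16 × 0.105 ≈ 1.7 |
| 32 | 5 | 36.0% | 36.6% | 5 × 0.006 ≈ 0.03 |
| 32 | 16 | 36.0% | 38.5% | 16 × 0.025 ≈ 0.4 |

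With 16 tests, Holm rejected more than Bonferroni in about 8%, 21%, 44% and 65% of trials for 5, 8, 12 and 16 true effects. In no simulated trial did Bonferroni reject a hypothesis that Holm did not.

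**Realised familywise error.** In a similar simulation (80% power per true effect at the unadjusted 5% level, correlation 0.3, 16 tests), it was 4.4% for both methods with no true effects. With 8 true effects it was 2.4% for Bonferroni and 3.3% for Holm.

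**Which row fits this trial.** The secondary outcomes named in the Background hypotheses correspond to about five rows of Table 1: time in range, quality of life, self-efficacy, depression and anxiety. Of the other 11 efficacy rows, seven are blood pressure, lipids and BMI. Twelve responders would require at least three of those seven to respond (12 − 5 − 4 = 3), and 16 would require all of them.

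**The case against.** The strongest objection is that this is a preference. Bonferroni is valid, simple and conservative, the sentence contains no mistake, and nothing about the primary analysis turns on it. That stands, and it sets the weight of the point. What remains is that the article positively names a method for which an at least equally powerful replacement exists under the same guarantee.

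Four stronger readings are tempting, and the documents do not support them:

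- *The plan applies Bonferroni to 16 outcomes at 0.0031.* The article gives neither figure. Sixteen is a count from Table 1 with adverse events left out, and the family may be defined in a fuller document that is not shown.
- *Holm is free.* A Bonferroni level yields simultaneous confidence intervals directly, whereas Holm has no equally simple counterpart. The article mentions 95% intervals for dichotomous outcomes but promises no multiplicity-adjusted ones, so nothing planned is lost. Unadjusted intervals beside Holm-adjusted p-values can still appear to disagree.
- *The error rate is identical.* The 5% bound is the same, but Holm uses more of it when some effects are real.
- *The hypothesised outcomes are where most power is lost.* With about five responders the gain is among the smallest in the table. The larger gains need 12 to 16 outcomes to respond.

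**Conclusion.** The point holds as an efficiency improvement. For any family, Holm controls the familywise error at the same 5% bound under any dependence, never rejects fewer hypotheses than Bonferroni and sometimes rejects more. That part rests on no assumption about this trial.

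The size does rest on assumptions: 16 or 32 tests, equal effects of 0.535, correlation 0.3 and 55 per arm. If only the outcomes named in the hypotheses respond, the gain is about 1.5 percentage points of power per true effect with 16 tests, and about 0.6 points with 32. It reaches about 6 points only if 12 of 16 respond, and about 10 if all 16 do.

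A reader might infer that the planned adjustment is wrong or endangers the trial's conclusions. It does neither: Bonferroni is valid, and the primary outcome and the sample size of 138 are unaffected.

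**What to change.** In the Data analysis section, replace *The Bonferroni method* with *The Holm step-down (Bonferroni-Holm) procedure* and leave the rest of the sentence alone. Apply it to the same set of tests the sentence now covers. Do not use the change to narrow the adjustment to week-24 outcomes, because the present wording can also reach the week-12 comparisons and the moderator interactions.

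Add that 95% confidence intervals reported beside adjusted p-values are not adjusted for multiplicity.

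The cost is a change of phrase and one added sentence, with no extra patients or data. The price is the loss of simple matching simultaneous intervals, which the plan does not promise. The change should be made before unblinded results are seen.
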